#### *Step 1: Watchful waiting*

The first 3 months consist of watchful waiting, because depressive symptoms often disappear spontaneously over time [26]. After inclusion and obtaining informed consent, patients are invited by their care manager for an introductory consultation. During this consultation patients will get acquainted with the care manager and they will receive an information brochure about mild depression with simple advices on how to cope with mild depressive symptoms. Patients will be informed about the stepped-care program and its rationale. In this step, no therapeutic intervention will take place.

#### *Step 2: Guided self-help treatment*

During this step, participants are offered a self-help course that is specially designed for patients with a chronic physical illness and depressive complaints [38]. During a visit to the general practice, the care manager will give the patient all necessary materials and explain the self-help course. Participants can work through the course at their convenience. In doing so, they will be supported by their care manager, who will contact them every other week by phone to monitor their progress. If it is clear that after two weeks the patient has not started the course yet, the care manager will use motivational interviewing techniques by phone to activate the patient. When this does not have the intended activating effect on the patient after two more weeks, the care manager invites the patient to come to the practice to discuss the current depressive symptoms (a PHQ-9 will be administered). When depressive symptoms still exist, patients are offered to progress early to step 3.

#### *Step 3: problem-solving treatment*

In this step, participants are offered Problem Solving Treatment (PST) by the care manager. PST is a brief cognitive behavioural intervention that focuses on practical skill building. It consists of a maximum of 7 sessions during which the stages of problem solving are explained and then applied to problems encountered in daily life. The goal of PST is to help patients regain control of their lives [39,40].

#### *Step 4: Referral to general practitioner*

Participants with continuously elevated PHQ-9 scores after 9 months will be referred to their general practitioner by the care manager for further assessment of their depressive symptoms. The GP receives a summary of the treatment provided to discuss with their patient.

#### Usual care

In the usual care practices, practice nurses and GPs will be blinded to which patients are participating in the study. They will not receive any training and will provide care as usual to all their patients according to existing clinical guidelines [41-43]. Participants in the usual care group will have unrestricted access to care as normally provided by their general practitioner. Their healthcare uptake (including use of prescribed medication) will be recorded.

### Training of the practice nurses

In the intervention practices, the practice nurses who are going to provide the stepped-care treatment will attend a two day training. This training focuses on how to implement the stepped-care program, how to provide guidance with the self help course using motivational interviewing techniques and how to provide the PST. The motivational interviewing techniques and the PST will be taught by a professional trainer. Before the trial starts, the trained practice nurses will perform two practice sessions of PST by telephone. These sessions will be audio taped and evaluated by the training staff to detect possible competence and/or adherence issues. During the trial, all practice nurses are regularly supervised by the training staff. Nurses can also contact the training staff to discuss any questions or problems, should they arise. When practice nurses have previously received training in motivational interviewing and/or PST, they are offered to follow a personalized training program.

### Outcomes

The primary clinical outcome is the cumulative incidence of DSM-IV major depressive disorder after 12 months according to the Mini International Neuropsychiatric Interview (MINI) [33,37]. The MINI will be administered by telephone at baseline and after 6 and 12 months after baseline by qualified research assistants.

Depression severity will be measured using the PHQ-9 [32,44]. The PHQ-9 is a widely used validated instrument to measure depression symptoms in general practice.

Quality of life will be measured using the EuroQol (EQ-5D) [45]). The obtained EQ-5D scores will be used to calculate utilities according to the Dutch tariff. QALYs will be calculated using the area-under-the-curve method with linear interpolation between time points.

For the economic evaluation, costs will be measured using the TiC-P questionnaire [46]. Costs that will be included are costs for healthcare utilization, informal care, and work absenteeism and presenteeism. Medication use will be retrieved from the patient’s pharmacy. If available, Dutch guideline prices will be used to value resource use. Medication use will be valued using prices of the Royal Dutch Society for Pharmacy. Lost productivity costs will be calculated according to the friction cost approach (friction period 154 days) using the mean age- and sex-specific income of the Dutch population. According to the friction cost approach a sick employee is replaced after a certain amount of time (the friction period) after which there are no lost productivity costs anymore. All costs will be adjusted to the year in which most data is collected using consumer price indices.

All secondary outcomes mentioned above will be administered at baseline, 3, 6, 9 and 12 months after inclusion through web-based questionnaires. If patients do not have access to the internet or prefer hard copies, we will provide these. In the intervention group, the PHQ-9 will also be administered by the nurse in the general practice for clinical monitoring and adjusting treatment when necessary.

Other secondary clinical outcomes include blood pressure, low-density lipoprotein (LDL) cholesterol and glycosylated haemoglobin (HbA1C). These outcomes will be measured at baseline and at 12 months follow-up and are performed as part of the usual care for this group of patients. Therefore, patients do not undergo any extra physical measurements.

To be able to control for possible confounders, demographics will be measured at baseline, along with personal and family history of mood disorders, using a subset of the Diagnostic Interview Schedule (DIS) [47]. The occurrence of co-morbid chronic illnesses will be assessed with the Dutch questionnaire chronic illnesses [48] at baseline and after 6 and 12 months, as well as locus of control [49]and social support [50]. All these measurements were previously used for the same purposes in the West Friesland Study [51]. In addition to this, anxiety symptoms will be measured at baseline, 3, 6, 9 and 12 months by the Hospital Anxiety and Depression Scale- Anxiety (HADS-A) [52].

After 12 months the uptake of the stepped-care program will be evaluated. The number of contacts with the care manager, the number of PST sessions, antidepressant use, and the number of referrals to the GP will be assessed by the care manager in the intervention group. Mental health care utilization outside the general practice will be assessed using the TiC-P questionnaire [46].

A process evaluation will be performed in which the barriers and facilitators of the stepped-care program and the experiences with the program will be evaluated. This will be done by organizing focus groups among volunteering patients, general practitioners and primary care nurses. In addition, satisfaction with the received care will be measured in all patients after 12 months by using the CSQ [53,54]. An overview of all measurements and instruments is provided in Table 1.

**Table 1 T1:** Overview of all measurements and instruments

	**screening**	**baseline**	**3 months**	**6 months**	**9 months**	**12 months**
Depression symptoms (PHQ-2)	**x**					
Demographics		**x**				
Depression symptoms (PHQ-9)		**x**	**x**	**x**	**x**	**x**
Clinical depression (MINI)		**x**		**x**		**x**
Health care costs (Tic-P)		**x**	**x**	**x**	**x**	**x**
Quality of life (EQ-5D)		**x**	**x**	**x**	**x**	**x**
Anxiety (HADS-A)		**x**	**x**	**x**	**x**	**x**
Personal and family history (DIS)		**x**				
Social support		**x**		**x**		**x**
Existing chronic illnesses		**x**		**x**		**x**
Locus of control		**x**	**x**	**x**	**x**	**x**
Satisfaction with provided care (CSQ)						**x**

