### Statistical analyses

Baseline data will be presented comparing the two treatment groups.

All analyses will be on an intention-to-treat basis. Differences between the stepped-care group and the usual care group will be tested using mixed model analyses. To test the cumulative incidence of depression over time, logistic mixed model analysis will be used. The obtained odds ratio describes the reduction in the risk of a MINI/DSM-IV depressive disorder in the intervention group relative to the control group. Linear and logistic mixed models (depending on the outcome) will also be used to test differences in symptoms of depression and anxiety and quality of life between both groups over time. If necessary, the models will be adjusted for confounders.

Sub group analyses will be performed to check for an interaction effect between depression severity at baseline and improvement in depressive symptoms at 12 months.

In case of unequal distributions of demographic variables between the two treatment groups, multivariate analyses techniques will be used to correct for these differences.

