#### Economic evaluation

Both a cost-effectiveness analysis and a cost-utility analysis will be performed. Missing cost and effect data will be imputed using multiple imputation according to the MICE algorithm developed by Van Buuren [56]. The results of the imputed datasets will be pooled using Rubin’s rules [57]. Costs typically have a highly skewed distribution. Policy makers want to have information on the difference in mean total costs between the two treatment groups in order to be able to estimate the total health care budget needed for a specific condition [58]. Therefore, bias-corrected and accelerated bootstrapping with 5000 replications will be used to estimate 95% confidence intervals around the mean difference in total costs between the treatment groups. Incremental cost-effectiveness ratios (ICERs) will be calculated by dividing the difference in mean total costs between the treatment groups, by the difference in mean effects between the treatment groups. Bootstrapping will also be used to estimate the uncertainty surrounding the ICERs, which will be graphically presented on cost-effectiveness planes. Cost- effectiveness acceptability curves will be estimated as well. Cost-effectiveness acceptability curves show the probability that the stepped-care program is cost-effective in comparison with usual care for a range of different ceiling ratios (i.e. the willingness to pay for 1 extra recovered patient), thereby showing decision uncertainty [59].

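### The QALY area includes baseline EQ-5D, but the cost-utility effect is given as a difference in group means with no adjustment for baseline utility named

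*Protocol article*

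**What the plan says.** The Outcomes section derives utilities from the EQ-5D with the Dutch tariff and states that "QALYs will be calculated using the area-under-the-curve method with linear interpolation between time points". On timing it says: "All secondary outcomes mentioned above will be administered at baseline, 3, 6, 9 and 12 months after inclusion". Table 1 likewise marks the EQ-5D at baseline and at all four follow-ups.

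The Economic evaluation section announces that "Both a cost-effectiveness analysis and a cost-utility analysis will be performed". It names the imputation algorithm, the pooling rule, the type of bootstrap and its 5000 replicates. The bootstrap is used "to estimate 95% confidence intervals around the mean difference in total costs between the treatment groups", and the ICER divides the cost difference "by the difference in mean effects between the treatment groups". No regression or covariate is named for QALYs.

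The parent section, Statistical analyses, has two adjustment clauses. After describing the mixed models for the clinical outcomes and for quality of life over time, it says: "If necessary, the models will be adjusted for confounders". It then adds: "In case of unequal distributions of demographic variables between the two treatment groups, multivariate analyses techniques will be used to correct for these differences".

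**The concern.** Baseline utility is a pre-treatment value. It enters the QALY area directly as the first of five points, and indirectly because it predicts the other four. If the arms differ at baseline, part of that difference appears in a difference of mean QALYs although the intervention did not produce it. The ICER, the cost-effectiveness plane and the acceptability curve of the cost-utility analysis would all move with it. Precision that a variable already collected could supply is also given up.

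Imbalance is plausible here. Only about thirty practices take part. According to the Randomization section, practices are allocated before patients are recruited, and patients, GPs and nurses cannot be blinded. Under Recruitment, the GP screens the patient list using the file and personal knowledge of the patient. Selection could therefore differ by arm, on top of chance.

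**Working it through.** **Plan's own figure.** The article gives no figure for the QALY comparison. Its sample size, which supplies the inputs below, reproduces:
- 30% against 15%, two-sided 0.05, power 0.80, no continuity correction: 121 per group.
- Repeated measures, taking four per patient: 121 × (1 + 3 × 0.45)/4 = 71.1, so 71 per group (142 in total).
- Clustering: N = 142 × (1 + (N/30 − 1) × 0.05) solves at 176.7, so 177.
- Dropout: 177/0.75 = 236.

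**Inputs.** From the article: visits at 0, 3, 6, 9 and 12 months; 236 patients; 30 practices; practice ICC 0.05. The article states that ICC for the clinical outcome, and it is borrowed here. Assumed, because the article does not give them: utility SD of 0.15 to 0.25 and an equal correlation rho between any two visits of 0.30 to 0.75. The value 0.45 is the article's within-patient ICC, also stated for the clinical outcome.

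**Weights.** Five points a quarter-year apart give trapezoid weights 0.125, 0.25, 0.25, 0.25, 0.125. They sum to 1, and their squares sum to 2 × 0.015625 + 3 × 0.0625 = 0.21875.

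**Formulas** (in units of SD²):
- Slope of QALY on baseline utility: b = 0.125 + 0.875 rho. This is the expected share of a baseline gap that reaches the unadjusted QALY difference.
- Variance of the QALY: V = rho + 0.21875 (1 − rho).
- Share of variance explained by baseline: R² = b²/V.
- Ratio of adjusted to unadjusted SE: √(1 − R²).

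| rho | b | V | R² | SE ratio | SE cut | Shift, gap 0.03 | Shift, gap 0.05 |
|---|---|---|---|---|---|---|---|
| 0.30 | 0.388 | 0.453 | 0.33 | 0.82 | 18% | 0.012 | 0.019 |
| 0.45 | 0.519 | 0.570 | 0.47 | 0.73 | 27% | 0.016 | 0.026 |
| 0.60 | 0.650 | 0.688 | 0.61 | 0.62 | 38% | 0.020 | 0.033 |
| 0.75 | 0.781 | 0.805 | 0.76 | 0.49 | 51% | 0.023 | 0.039 |

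**How large a chance gap is ordinary.** The design effect is 1 + (236/30 − 1) × 0.05 = 1.343. The SE of the baseline difference is SD × √(4/236 × 1.343) = 0.151 × SD:
- SD 0.15: SE 0.023, 95% range ±0.044.
- SD 0.20: SE 0.030, 95% range ±0.059.
- SD 0.25: SE 0.038, 95% range ±0.074.

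A gap of one SE or more occurs in about one trial in three.

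**Simulation** (4000 runs, 30 practices of 8, ICC 0.05, SD 0.20, rho 0.45, no treatment effect). A baseline shift d was imposed, with rho × d at later visits. The unadjusted difference moved by 0.016 for d = 0.03 and by 0.026 for d = 0.05. The adjusted difference stayed at 0.000. The SE fell from about 0.0247 to 0.0160, a ratio of 0.65. That 35% fall exceeds the 27% in the table because the simulated practice effect is constant over visits. Practices then carry 0.05/0.570 = 0.088 of the QALY variance, and adjustment removes part of that too.

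**Scale against the effect sought.** Purely as an assumption, let a depressive episode cost 0.2 to 0.4 in utility for 3 to 6 months. The planned 15-point reduction is then worth 0.15 × 0.2 × 0.25 = 0.0075 to 0.15 × 0.4 × 0.5 = 0.03 QALYs per patient. The shift from a 0.03 gap (0.012 to 0.023) is of the same order.

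**The case against.** The strongest objection is that this is silence, not error. A reader might infer that the plan commits to an unadjusted QALY difference. The text does not say so. It gives the usual definition of an ICER, an adjusted mean difference would satisfy that definition, and the article condenses a fuller plan that is not shown. This stands as a limit on how strongly the point can be put. It does not remove the point, because the section fixes the estimator in some detail and, as written, stops at group means.

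A second objection is that Economic evaluation is a subsection of Statistical analyses, so the adjustment clauses there might extend to it. They do not rule adjustment out. But one is conditional and attached to the mixed models, and the other concerns demographic variables. Neither names baseline utility or is carried into the ICER.

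Third, a reader might infer that a baseline gap makes the cost-utility result invalid. Under chance imbalance it does not. The contrast is unbiased over repeated trials, and its standard error already contains baseline variation. At SD 0.20 and rho 0.60 that SE is 0.20 × √(0.688 × 4/236 × 1.343) = 0.025, larger than the 0.020 shift from a one-SE gap. A bootstrap that respects practices would carry that uncertainty. What remains is conditional bias in the realised trial and avoidable loss of precision.

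Lastly, the sizes depend on assumed values. If correlation decays with time, baseline explains less of the area than the table shows.

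**Conclusion.** The point holds as a recommended improvement to a secondary, economic analysis. It is not an error that must be fixed before the trial can be interpreted. The QALY area contains baseline utility with weight 0.125, the effect is defined as a difference in group means, and no clause that reaches it adjusts for that value.

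At assumed correlations of 0.30 to 0.75, about 0.4 to 0.8 of a realised baseline gap passes into the QALY difference, and adjustment would cut the standard error by 18% to 51% (27% at 0.45). The likely size of a chance gap also depends on the assumed SD and the borrowed practice ICC.

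Recruitment after unblinded allocation could add systematic imbalance, but the article gives nothing from which to size it. Adjustment would remove only part of a gap that persisted in full at every visit. With weights summing to 1, the unadjusted shift would then be d and the adjusted shift d × (1 − 0.519) = 0.48d at rho 0.45.

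The primary outcome, its analysis and the sample size are untouched.

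**What to change.** In Economic evaluation, state that the QALY difference is the treatment coefficient from a regression of 12-month QALYs on arm and baseline EQ-5D utility, with clustering by practice accounted for by a mixed model or by resampling whole practices. Fit it within each imputed data set and bootstrap replicate, and use that coefficient for the cost-utility ICER, plane and acceptability curve. A patient-level regression that ignores practices would not suit a cluster trial.

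The cost is a sentence or two in the analysis text. Baseline EQ-5D is already collected, and no extra patients are needed. Fixing this in advance also avoids deciding on adjustment after the baseline table has been seen.

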### Sample size

The trial is powered to detect a difference of 15% in the cumulative incidence rates of MINI/DSM-IV depressive disorder between the conditions after 1 year. The incidence rate is expected to be 30% in the usual care group and 15% in the intervention group based on findings from earlier studies [2,25,26]. Using a standard sample size calculation, 121 patients per group are needed, assuming a power of 0.8 and an alpha of 0.05. However, we need to correct for the fact that there is a multilevel setting with three levels: GPs, patients and measurements. Therefore we have first adjusted for the fact that we do not have one, but multiple measurements per patient. Assuming these measurements are clustered with an intraclass correlation (ICC) of 0.45, seventy-one patients per group are needed. Subsequently, we adjusted this figure further for clustering of patients within GP practices. Assuming an ICC of 0.05 for clustering of patients within the 30 GP practices, we need a total of 177 patients. Finally, we adjusted for a dropout rate of 25%, which means that 236 patients (118 patients per group) need to be included in this trial. This power calculation is based on the method described by Twisk in 2006 [55].

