### Recruitment

To recruit eligible patients, in all participating general practices an initial list of adult patients with DM2 and/or CHD is composed, based on diagnoses classified using the ICPC (International Classification of Primary Care) in the medical electronic information system; see Additional file 1 for details. This list is given to the general practitioner, who checks the preset inclusion criteria and excludes all patients that fulfill our preset exclusion criteria, based on the medical file and experiences with the patient. All remaining eligible patients will receive a letter on behalf of the general practitioner, in which all (at that point) necessary information regarding the study, as well as an invitation to participate is included. When patients consider to participate, they are asked to fill out a two question screening form (Patient Health Questonnaire-2, or PHQ-2 [34]) that will be provided with the information letter and send it back using a prestamped envelope. All patients with a PHQ-2 score of 2 or more [34,35] will receive additional information from the research team. Based on this information informed consent is obtained for a telephone interview. During this interview the Dutch version of the PHQ-9 [36] and the MINI [37] will be administered. Patients scoring 6 points or more on the PHQ-9, but not having a major depression according to the MINI are eligible for the study and will be asked for written informed consent to participate. From this point on, patients are either enrolled in the stepped-care program or will receive care as usual, depending on the general practice at which they are registered. An overview of the study design and patient flow is provided in Figure 1.

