### Intervention

The intervention is modelled after the flexible stepped-care intervention developed by van ‘t Veer-Tazelaar et al. [26]. After receiving a specially developed training, practice nurses in the intervention practices will act as care managers and work together with the General Practitioner (GP) to provide the stepped-care treatment. The care managers coordinate the execution of the stepped-care program that consists of four evidence-based subsequent treatment steps, lasting 3 months each. The flow of participants in the intervention group through the stepped-care program depends on their depressive symptom level, measured using the PHQ-9 every 3 months during 1 year. Participants who still have elevated depressive symptom levels (i.e. a PHQ-9 score of 6 or more) after concluding a step, are offered participation in the next step. A score below the cut off point results in a period of watchful waiting until an elevated PHQ-9 score indicates the need for the subsequent step of the intervention. By only offering more intensive treatment to patients who continue to have elevated depressive symptom scores, it is expected that patients will receive treatment tailored to their needs and that available resources are more efficiently used by providing the more intensive treatments only to those who need this. Patients who meet the MINI diagnostic criteria for major depression at baseline or at 3, 6, 9 or 12 months are referred to their GP by the practice nurse for further assessment. The following treatment steps are offered to participants:

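### The sample size takes a repeated-measures discount that fits four measurements per patient, but the outcome is a 12-month cumulative MINI status and the MINI is scheduled twice after baseline: power is about 57%, at most about 71%, not 80%

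*Protocol article*

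**What the plan says.** All references are to the protocol article.

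- **Target (Sample size).** "The trial is powered to detect a difference of 15% in the cumulative incidence rates of MINI/DSM-IV depressive disorder" after one year. "The incidence rate is expected to be 30% in the usual care group and 15% in the intervention group". A standard calculation with alpha 0.05 and power 0.8 gives 121 per group.
- **Repeated-measures step (Sample size).** "Assuming these measurements are clustered with an intraclass correlation (ICC) of 0.45, seventy-one patients per group are needed". The section says there are multiple measurements per patient but not how many.
- **Clustering and dropout (Sample size).** An ICC of 0.05 over 30 practices brings the total to 177. A 25% dropout allowance follows, "which means that 236 patients (118 patients per group) need to be included in this trial".
- **Endpoint (Outcomes).** "The primary clinical outcome is the cumulative incidence of DSM-IV major depressive disorder after 12 months".
- **MINI schedule (Outcomes).** "The MINI will be administered by telephone at baseline and after 6 and 12 months after baseline by qualified research assistants". Table 1 agrees, with marks at baseline, 6 and 12 months only.
- **Baseline status (Recruitment).** "Patients scoring 6 points or more on the PHQ-9, but not having a major depression according to the MINI are eligible".
- **Conflicting text (Intervention).** "Patients who meet the MINI diagnostic criteria for major depression at baseline or at 3, 6, 9 or 12 months are referred to their GP".
- **Analysis (Statistical analyses).** The cumulative incidence over time is to be tested with a logistic mixed model.

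**The concern.** Averaging several correlated measurements of the same quantity lowers the number of patients needed, provided each measurement carries the full treatment difference. The cut from 121 to 71 relies on that. The quantity sized here is different: whether a patient has met MINI criteria by 12 months. It is known once per patient, and the instrument that establishes it is scheduled twice after baseline. Four follow-ups is the schedule of the questionnaires (PHQ-9, EQ-5D, HADS-A), not of the MINI in Table 1.

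The 80% power is the only justification given for 236 patients. If the discount is not available, the trial is considerably more likely than stated to miss a true halving of incidence, and readers of a null result would be working from the wrong error rate.

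**Working it through.** **Inputs.** From Sample size: 30% and 15%; alpha 0.05 (taken as two-sided, which reproduces 121); power 0.80; within-patient ICC 0.45; practice ICC 0.05; 30 practices; 25% dropout. From Outcomes and Table 1: two post-baseline MINIs. Equal cluster sizes are assumed.

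**1. Reproducing the plan's chain**

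- Two proportions, pooled variance under the null: n = [1.96 x sqrt(2 x 0.225 x 0.775) + 0.8416 x sqrt(0.30 x 0.70 + 0.15 x 0.85)]^2 / 0.15^2 = 120.5, so 121 per group. Matches.
- Repeated measures: 121 x [1 + (T - 1) x 0.45] / T, where T is the number of measurements per patient.

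| T | Factor | Patients per group |
|---|---|---|
| 1 | 1.000 | 121 |
| 2 | 0.725 | 87.7 |
| 3 | 0.633 | 76.6 |
| 4 | 0.5875 | 71.1 |
| 5 | 0.560 | 67.8 |

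  Only T = 4 gives the stated 71.
- Practice clustering: N = 142 x [1 + (N/30 - 1) x 0.05], so N = 142 x 0.95 / (1 - 142 x 0.05/30) = 176.7, i.e. 177. That is 5.9 patients per practice and a design effect of 1.245. Matches.
- Dropout: 177 / 0.75 = 236. Matches.

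**2. Power of 236 enrolled for 30% versus 15%**

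Effective patients per group: 177 / 1.245 / 2 = 71.08. Crediting T measurements divides this by the factor above to give n. Then power = Phi{[0.15 x sqrt(n) - 1.1575] / 0.5809}, where 1.1575 = 1.96 x sqrt(2 x 0.225 x 0.775) and 0.5809 = sqrt(0.30 x 0.70 + 0.15 x 0.85).

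| Measurements credited | n per group | Power at 177 evaluable | Power if nobody drops out |
|---|---|---|---|
| 1 (12-month status) | 71.08 | 57% | 67% |
| 2 (scheduled MINIs) | 98.05 | 71% | 80% |
| 4 (as in the plan) | 120.99 | 80% | 88% |

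The no-dropout column uses 236/30 = 7.87 patients per practice, a design effect of 1.343 and 236 / 1.343 / 2 = 87.8 effective patients per group before any repeated-measures credit.

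Counting baseline as a third measurement would give 77%, but every participant is MINI-negative at baseline by eligibility, so baseline carries no outcome information.

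**3. Difference detectable with 80% power at 177 evaluable**

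Solving the same expression for the intervention rate, with usual care at 30%:

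- one status: 11.2%, a difference of 18.8 points;
- two measurements: 13.6%, a difference of 16.4 points.

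**4. Would more MINI visits rescue the discount?**

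A patient who is positive by 6 months is also positive by 12 months, so the earlier status is nested in the later one and shows a smaller difference. For scale, take a constant hazard, which is an assumption and not in the protocol. At 6 months the cumulative rates are 1 - sqrt(0.70) = 16.3% and 1 - sqrt(0.85) = 7.8%, a difference of 8.5 points instead of 15. With 71 effective per group and an unpooled normal approximation, power is about 59% for the 12-month status alone, about 55% for the average of the 6- and 12-month statuses, and about 52% for the average of statuses at 3, 6, 9 and 12 months. Under this assumption, simple averaging loses power.

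**The case against.** **The number four is not in the text.** Correct. It is inferred from 121 and 71. No other whole number fits the standard formula, but the point should be put as an inference, and the method source cited in Sample size is not at hand.

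**The protocol also points to four MINI occasions.** The referral sentence in Intervention names 3, 6, 9 and 12 months. A reader might infer that the MINI is beyond doubt given only twice, or that this sentence vindicates T = 4. Neither follows. Outcomes and Table 1 are the explicit measurement schedule and agree on two, so the documents contradict each other and must be reconciled. Four visits would establish the cumulative status more closely in time; they would not supply four estimates of a 15-point difference.

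**The planned analysis is longitudinal.** This stands in part. Statistical analyses specifies a mixed model over time, and Sample size names measurements as a level. It would therefore be too strong to say that 57% is the only defensible figure. The averaging in step 4 is also not the planned model and rests on an assumed hazard. On the plan's own formula and scheduled visits the credit is at most two measurements, so 71% is the upper figure.

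**Dropouts may still contribute.** Under intention to treat with a mixed model, a patient seen at 6 but not at 12 months is not wholly lost. With no dropout at all, two measurements would reach 80%, but one status still gives only 67%. The 25% allowance is the plan's own.

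**Each step computes correctly.** Also true. The fault is an assumption that does not match the endpoint and schedule; there is no slip in the arithmetic.

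**Conclusion.** The point holds. The reduction from 121 to 71 per group needs four measurements per patient, each carrying the full difference. The primary outcome is one cumulative status at 12 months, and the MINI is scheduled twice after baseline. At the plan's 177 evaluable patients, power for 30% versus 15% is about 57% for the single status and at most about 71% with two MINIs credited. The chance of missing the planned effect is thus about 43%, or at least about 29%, instead of 20%.

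This rests on the plan's own rates, ICCs, 30 practices and 25% dropout, with two-sided alpha and equal clusters; unequal clusters would lower power further.

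A reader might go on to infer that the trial must enrol some particular larger number. The documents do not settle one. For a single status the plan's steps give about 402 enrolled at 5.9 evaluable patients per practice, but about 514 if practices stay at 30. The defect is in the stated power, and it can be corrected without choosing between those figures.

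**What to change.** In Sample size:

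1. State how many MINI measurements per patient the calculation assumes, and reconcile Intervention with Outcomes and Table 1 so that the number matches one schedule.
2. Remove the repeated-measures reduction for the 12-month cumulative endpoint. If the longitudinal mixed model is the primary test, credit at most two measurements.
3. Restate the power of 236 enrolled for 30% versus 15% as about 57% (at most about 71%), with 80% power only for about 30% versus 11% (30% versus about 13.6% with two measurements).

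The cost is a rewritten paragraph and a less favourable stated power. The correction itself requires no added enrolment, although 236 would then no longer be presented as giving 80% power for a 15-point difference.
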